## Abstract

**Background:**

Persistent atrial fibrillation frequently shows multiple different electrophysiological mechanisms of induction. This heterogeneity causes a low success rate of single procedures of ablation and a high incidence of recurrence. Surgical ablation through bilateral thoracotomy demonstrates better results after a single procedure. Prospective observational studies in inhomogeneous populations without control groups report a remarkable 90% of success with hybrid or staged procedures of surgical ablation coupled with catheter ablation. In this trial, we will examine the hypothesis that a staged approach involving initial minimally invasive surgical ablation of persistent atrial fibrillation, followed by a second percutaneous procedure in case of recurrence, has a higher success rate than repeated percutaneous procedures.

**Methods/Design:**

This is a controlled (2:1) randomized trial comparing use of a percutaneous catheter with minimally invasive transthoracic surgical ablation of persistent atrial fibrillation. The inclusion and exclusion criteria, definitions, and treatment protocols are those reported by the 2012 Expert Consensus Statement on catheter and surgical ablation of atrial fibrillation. Patients will be randomized to either percutaneous catheter (*n* = 100) or surgical (*n* = 50) ablation as the first procedure. After 3 months, they are re-evaluated, according to the same guidelines, and receive a second procedure if necessary. Crossover will be allowed and data analyzed on an “intention-to-treat” basis. Primary outcomes are the incidence of sinus rhythm at 6 and 12 months and the proportions of patients requiring a second procedure.

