### Assessment of recurrence

The recurrence will be assessed by clinical follow-up at 1, 3, 6, 9, and 12 months with 12-lead ECG + 24 Holter monitoring. Transthoracic echocardiography will be also performed to record the presence of an atrial contraction in case of sinus rhythm. Quality of life will be assessed by a modified 36-item Short Form Health Survey and the Euro 5D questionnaire. The primary outcomes include the freedom from AF at 12 months, as detected by a 12-lead ECG and a 24-hour Holter examination after 3, 6, and 9 months of follow-up, and the occurrence of a second ablation procedure. The secondary outcomes include the duration of the procedures, freedom from any documented atrial arrhythmia, incidence of procedural complications, any late complication related to the procedures, and quality of life.

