### Statistical analysis

Randomization will be performed by using currently available computer software. Sample size is based on the hypothesis that the success rate of the first procedure will be approximately 70% for the surgical cases and 35% to 40% for the PCA cases. At the end of the interventions, the number of patients in SR should be equivalent in the two groups, whereas the proportions of those submitted to a second procedure, either percutaneous or surgical, should differ significantly. Variables will be analyzed with an intention-to-treat method. The three possible results of this study are described in Table 1. A flow chart depicting the most favorable result in which the power of the test is 98% is shown in Figure 1. Data will be expressed as mean ± SD and 95% confidence limits, as appropriate. Comparisons between patient groups will be performed with the Mann–Whitney test for continuous variables and the χ^2^ test for categoric variables. The *z* test and the odds ratio will be used for differences between proportions of patients receiving repeated procedures in the two groups. A value of *P* < 0.05 will be considered statistically significant. Time-to-event distributions will be estimated by the Kaplan-Meier method and compared with the log-rank test. The Cox proportional hazards model will be used to identify independent risk factors for recurrences. Stepwise selection procedure will be adopted. A value of *P* < 0.05 will be considered significant for variable entry for stepwise selection. Analyses are performed with the SPSS 18.0 software package (SPSS, Inc, Chicago, IL, USA).

**Table 1 T1:** Anticipated results for different success rates of first PCA procedure

**% of SR in the PCA group after first procedure**	**35%**	**45%**	**50%**
**χ**^ **2 ** ^**test for first procedure**	*P* < 0.0001	*P* = 0.007	*P* = 0.03
Power of the test	99%	84%	65%

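### The abstract and Methods name different primary outcomes under one unadjusted 0.05 threshold; if any one suffices, overall error can reach about 10% (two primaries) or 14% (three)

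*Protocol article*

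**What the plan says.** The primary outcomes are listed twice, differently.

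- Abstract, Methods/Design: "Primary outcomes are the incidence of sinus rhythm at 6 and 12 months and the proportions of patients requiring a second procedure". If each time point is tested, that is three comparisons.
- Methods, Assessment of recurrence: "The primary outcomes include the freedom from AF at 12 months" (with the assessment schedule), "and the occurrence of a second ablation procedure". That is two comparisons, and 6-month rhythm is not a separate outcome.

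Statistical analysis gives one general criterion: P "< 0.05 will be considered statistically significant". It states no order of testing, no division of the 0.05 and no rule on whether one or all primaries must succeed.

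The trial is sized on the assumption that "the success rate of the first procedure will be approximately 70% for the surgical cases and 35% to 40% for the PCA cases". Table 1 converts these rates into second-procedure fractions and gives power of 99%, 84% and 65% for PCA success of 35%, 45% and 50%. The same section expects that "the number of patients in SR should be equivalent in the two groups". It looks for a significant difference only in how many patients go on to a second procedure. The closing paragraph of the Background, however, hypothesizes a higher 12-month success rate with the staged surgical approach.

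**The concern.** With two or three primaries each judged at 0.05, the 5% applies to each test and not to the trial's overall claim. The plan leaves two routes to a favorable headline: fewer second procedures (the sized comparison and the overall hypothesis that opens the Methods) and better rhythm at 12 months (the Background hypothesis). The abstract's 6-month time point would add a third. Because the two lists differ, the choice of which result counts could be made after the data are seen, which would weaken any confirmatory claim. The power in Table 1 would also be too high if the 0.05 later had to be shared between outcomes.

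**Working it through.** **Inputs.** 100 PCA and 50 surgical patients; surgical success 70%; PCA success 35%, 45% or 50% (Table 1); threshold 0.05. Sidedness is not stated, so two-sided is assumed. The correlation between primaries is not given, so a range is used.

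**1. The plan's own power.** Normal approximation, pooled variance under the null, no continuity correction:

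power = Φ{(|p₂ − p₁| − z·SE₀)/SE₁}, where SE₀ = √[p̄(1 − p̄)(1/100 + 1/50)], SE₁ = √[p₁(1 − p₁)/100 + p₂(1 − p₂)/50] and z = 1.96.

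- 35%: p̄ = 70/150 = 0.4667, SE₀ = 0.0864, SE₁ = 0.0805; (0.35 − 1.96 × 0.0864)/0.0805 = 2.24, power 98.8%.
- 45%: p̄ = 80/150 = 0.5333, SE₀ = 0.0864, SE₁ = 0.0817; (0.25 − 1.96 × 0.0864)/0.0817 = 0.99, power 83.8%.
- 50%: p̄ = 85/150 = 0.5667, SE₀ = 0.0858, SE₁ = 0.0819; (0.20 − 1.96 × 0.0858)/0.0819 = 0.39, power 65.1%.

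These match the stated 99%, 84% and 65%. Table 1 is therefore a single test at two-sided 0.05, with nothing set aside for multiplicity.

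**2. Overall error if any one primary suffices and every null is true.** Under independence:

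- two tests: 1 − 0.95² = 9.75%
- three tests: 1 − 0.95³ = 14.26%

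For jointly normal two-sided tests, independence is the worst case. With a common absolute correlation r (simulation, 2 million draws per setting, probability that any |Z| exceeds 1.96):

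| r | two primaries | three primaries |
|---|---|---|
| 0.3 | 9.5% | 13.6% |
| 0.5 | 9.1% | 12.5% |
| 0.7 | 8.3% | 10.9% |
| 0.8 | 7.8% | 9.8% |
| 0.9 | 7.0% | 8.4% |

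With unequal correlations (0.6–0.8 between the two rhythm time points, 0.3–0.7 between rhythm and second procedure), three primaries give 10.5% to 12.9%.

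These figures count false findings in either direction. False findings favoring surgery are about half: 1 − 0.975² = 4.9% and 1 − 0.975³ = 7.3% at independence, against 2.5% for one test.

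**3. Overall error if all primaries must be significant.** At most 5%, so no inflation.

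**4. Power if the 0.05 is split equally over two primaries.** With z = 2.2414 in the formula of step 1, the 45% case gives (0.25 − 2.2414 × 0.0864)/0.0817 = 0.69, power 75.5%. The 35% and 50% cases give 97.4% and 53.7%.

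**The case against.** The strongest reply has four parts.

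**The source is condensed.** This is a journal article, and a full protocol or SAP, not shown, may control multiplicity. That is fair as regards a missing adjustment, and the absence alone would be no finding. It does not explain why the article gives two different primary sets.

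**No any-one rule is written.** This is correct, and if all primaries had to differ there would be no inflation. But that reading does not fit the sizing. If final rhythm is the same in both groups, as Statistical analysis expects, the rhythm test is significant only about 5% of the time. A trial needing both results would then succeed at most about 5% of the time, and 99%, 84% and 65% could not describe its chance of success.

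**The section points to one confirmatory comparison.** Statistical analysis seeks a difference in second procedures only. Taken alone, it supports that reading. The Background, however, hypothesizes superiority at 12 months and the Methods make that outcome primary, so a significant rhythm result would also support the main claim.

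**The outcomes are related.** Rhythm at 6 and 12 months comes from the same patients, and a second procedure follows recurrence. This stands. A reader might infer that the error simply is 10% to 15%. The documents do not support that: those figures need independence and the any-one rule, and the upper one also needs the abstract's three-comparison reading, which the Methods do not share.

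**Conclusion.** The point holds in conditional form. The primary sets differ between abstract and Methods, and one unadjusted 0.05 threshold covers them without an order. If any one significant primary supports a positive claim, overall two-sided error can reach about 10% with two primaries or 14% with three. At correlations of 0.3 to 0.9 it is about 7–9.5% and 8–14%, above 5% at every correlation examined. This rests on two-sided tests, an assumed correlation range and a success rule that the plan's hypotheses imply but do not state. The Table 1 power is right for a single test at 0.05 and carries no multiplicity allowance. The correction should be made before results are known; Trial status says that recruitment is under way.

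**What to change.** 1. State the same primary set in the abstract and the Methods, with sinus rhythm at 6 months as a secondary outcome.
2. Name one first primary, taken from what the trial was sized on, at two-sided 0.05. Choose either failure of the first procedure or receipt of a second procedure. They are not the same outcome: the two treatment-group sections let some recurrences be managed without a second ablation, and the PCA section adds its own counting rule for a switch to rate control. Table 1 treats them as equal (0.65 = 1 − 0.35; 0.30 = 1 − 0.70), so its power carries over to second procedures only as far as that equality holds.
3. Test 12-month freedom from AF only if the first test is significant.
4. Name one test per outcome. The plan allows χ² or log-rank for rhythm. For the first primary, say whether a continuity correction applies, since the Table 1 power matches the uncorrected test.
5. Reconcile the Background's superiority hypothesis with the equivalence expected in Statistical analysis. A gated difference test cannot demonstrate equivalence.

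The cost is a few sentences. The fixed sequence keeps 5% overall and leaves the power of the sized comparison unchanged, whereas Bonferroni over two would cut it to about 97%, 75% and 54%. The downside is that 12-month rhythm superiority cannot be claimed if the first test fails. Because that is the Background's own hypothesis, the investigators should accept this ordering explicitly.

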**Discussion:**

The use of a staged strategy combining surgical and percutaneous approaches might be more favorable in treatment of persistent atrial fibrillation than the controversial single percutaneous ablation.

**Trial registration:**

ISRCTN08035058 Reg 06.20.2013

## Background

Persistent atrial fibrillation (PeAF) is defined as episodes of atrial fibrillation (AF) lasting more than 7 days or requiring an electric or pharmacologic cardioversion to restore the sinus rhythm (SR) [1]. PeAF is frequently caused by different coexistent electrophysiological mechanisms of induction [2]. This complex origin frequently requires the use of a combination of ablation techniques to achieve acceptable results. Indeed, pulmonary vein isolation (PVI) [3] and the ablation of complex fractioned atrial electrograms (CFAEs) [4] did not result in satisfactory results when used separately during percutaneous catheter ablation procedures (PCAs), whereas the rate of success increased to 74% after combining the two techniques and was 88% when ablation was repeated after 3 months [5]. The evaluation of treatment for PeAF is further complicated by the small number of patients with PeAf included in controlled trials [6]. Similar outcomes are observed for the surgical treatment of PeAF. For example, in the FAST trial (atrial fibrillation catheter ablation versus surgical ablation treatment) [7], surgical ablation achieved better results (65% versus 36%; *P* = 0.0022) than PCA in complex patients, whereas this trend was not confirmed in the cases with PeAf, who were a minority of those randomized.

Regardless of the mechanism involved, the majority of the sites of origin of PeAF are located in the posterior part of the left atrium, as this portion is easily encompassed by the box lesions created by surgical ablations [8]. As such, a staged approach may be a more suitable strategy, with use of percutaneous endocardial techniques only in case of failure of the surgical procedures. Recently, Pison [9] obtained a success rate of 90% in PeAf with a hybrid approach involving bilateral minimal surgical access and PCA. In this series, only 23% of the lines created surgically were not transmural, and 88% of the patients had the AF terminated by a posterior left atrial isolation. Comparable results were reported with staged [10] approaches of thoracoscopy or transabdominal pericardial [11] access and PCA.

In the present trial, we examine the hypothesis that a staged approach involving minimally invasive surgical ablation of persistent atrial fibrillation, followed by a second percutaneous procedure in cases of recurrence, will have a success rate at 12 months higher than repeated percutaneous procedures. According to the recently published European guidelines on surgical ablation of AF alone, we will select patients with a class IIb indication to surgery and use the class I bipolar radiofrequency as the energy source for the ablation [12].

## Methods

The overall hypothesis of this study is that an initial surgical procedure has a higher probability of success than an initial percutaneous ablation, and therefore, fewer patients will be submitted to a second ablation. The proposed therapies are currently accepted and considered Class II indications in the current European Society of Cardiology [13] and European Association of Cardiothoracic Surgery [12] guidelines for the treatment of PeAf. As such, their comparison complies with the Declaration of Helsinki for the Ethical Principles of Medical Research in human subjects. The Ethics Committee of the University of Magna Grecia in Catanzaro (Italy) gave full approval to the study without conditions. No external financial support exists. Full reimbursement of the cost of the therapies has already been granted by the Italian National Health System.

All participants will be required to sign an informed consent to adhere to the study. The Surgical Staged Approach (SSA) strategy consists of an initial minimally invasive surgical ablation, followed by a percutaneous catheter ablation if necessary. To avoid any possible bias introduced by the difference in surgical techniques, we will use only the bipolar radiofrequency using the Estech cobra fusion ablator (Estech is a Market brand of Atricure Inc West Chester 45069 Ohio USA) introduced through a right minimal thoracotomy. The control group will receive the current standard strategy of PCA. In the case of recurrence of the AF, the second procedure will be either percutaneous or surgical. The inclusion criteria and the protocols for managing the pharmacologic and anticoagulant therapy, the description of the surgical approach, and the technique of the percutaneous ablation are those indicated by the 2012 HRS/EHRA/ECAS expert consensus statement on catheter and surgical ablation of AF [12] and the European Guidelines for the treatment of lone AF [13].

### Inclusion criteria

• Patient age ≥18 years.

• Patients with persistent AF defined as at least one sustained episode lasting more than 7 days in the last 12 months.

• Patients with symptomatic AF that is refractory to at least one antiarrhythmic medication; symptomatic patients are those who have been aware of their AF at any time within the last 5 years before enrolment. Symptoms may include, but are not restricted to, palpitations, shortness of breath, chest pain, fatigue, left ventricular dysfunction, or other symptoms, or any combination of these.

• At least one episode of persistent AF must have been documented by ECG, Holter, loop recorder, telemetry, transtelephonic monitor, or implantable device within last 2 years of enrollment in this investigation.

• Patients must be able and willing to provide written informed consent to participate in this investigation.

• Patients must be willing and able to comply with all periablation and follow-up requirements.

### Exclusion criteria

• Patients with paroxysmal AF, defined as a sustained episode lasting <7 days.

• Patients with long-standing persistent AF lasting >1 year.

• Patients for whom cardioversion or sinus rhythm will never be attempted/pursued.

• Patients with AF secondary to a reversible cause.

• Patients with contraindications to systemic anticoagulation.

• Patients with left atrial size ≥55 mm (2-dimensional echocardiography, parasternal long-axis view).

• Patients with LA thrombi as demonstrated by transesophageal echocardiography (TEE).

### Interventions

#### *Antiarrhythmic therapy*

All antiarrhythmic drugs will be discontinued 5 half-lives before the procedure. In exceptional cases requiring strict rhythm management to control preoperative symptoms, this will be managed with intravenous esmolol. Amiodarone requires at least 8 weeks of suspension.

#### *Anticoagulant therapy*

Patients receiving warfarin will stop the medication and switch to LMW heparin, which will be maintained during the procedure but which can be controlled in case of major bleeding. The same applies to patients receiving apixaban, dabigatran, or rivaroxaban, to control the silent thromboembolism described during the creation of endocardial lesions [14]. If the patient is taking only aspirin, it need not be discontinued.

All patients will receive preoperative TEE echocardiograms to rule out the presence of left atrial thrombi and to determine the size, morphology, and flow pattern in the left atrial appendage.

### Staged surgical ablation group

Fifty patients will be randomized to surgical ablation of AF. The ablation procedure will be performed with the use of Estech cobra fusion, according to the manufacturer’s instructions and to the commonly described techniques [10,12,15]. Up to three applications will be allowed to ablate the left atrial box. Bidirectional block will be checked, and reasons for not obtaining it will be noted. Inducibility of AF at the end of the procedure will be recorded. Cardioversion will be allowed to restore SR. At the end of the procedure, the patient will be awakened and transferred to the ward. An interval of 3 months will be allowed after the initial ablation procedure, as per the Heart and Rhythm European Society Association/European Heart Rhythm Association/European Cardiac Arrhythmia Society expert consensus statement [13]. During this period, the recurrences of AF, atrial tachycardias, and atrial flutter will not be counted toward the primary or secondary end points. Antiarrhythmic medications may be continued for the first 3 months to avoid early recurrences. At 3 months, they must be stopped to assess recurrences. For patients continuing to have recurrence controlled by the therapy, it will be left to the preference of the investigator to continue the medical therapy or to refer the patient for a PCA.

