### Percutaneous catheter ablation group

One hundred patients will be randomized to PCA and treated according to the protocol of the referring center. In all cases, complete PVI must be at least attempted and confirmed by bidirectional block. The referring investigator can then add any of the current methods of PeAF treatment, including substrate modification with the infusion of isoproterenol to uncover non-PVI triggers and CFAE. Lines can be drawn at the discretion of the investigators. Inducibility of AF at the end of the procedure will be recorded. Cardioversion will be allowed to restore SR.

After the 3-month blanking period, it will be left to the investigator’s preference to refer the patients with PeAF recurrence to a second PCA procedure, surgical ablation, or switch to a rate-control approach. The latter will be counted as a failed repeated procedure.

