### Study limitations

No standard strategy is known for the percutaneous ablation of PeAF. In the PCA control group of our study, the choice of the initial technique will be left to the treating cardiologist (PVI, CFAE ablation with or without manipulation of the substrate, or rotor manipulation are frequently used in combination or in staged procedures). Insulated PVI is the least effective technique, whereas rotor modulation has been recently introduced and is not widely used. Thus, we expect that the majority of the patients in the control group will undergo a combination of PVI and CFAE ablation. In cases of failure in the surgical group, this choice will be dictated by the residual electrophysiological findings. This is a potential limitation of the study that may make comparison between the two groups difficult.

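### The month-3 antiarrhythmic stop and the option to stay on drug are written for the surgical arm only, so both primary outcomes can be judged under different drug rules by arm

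*Protocol article*

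**What the plan says.** Protocol article, Staged surgical ablation group: antiarrhythmic drugs are permitted during the first three months, and then "At 3 months, they must be stopped to assess recurrences". For a patient whose recurrence is controlled by therapy, "it will be left to the preference of the investigator to continue the medical therapy or to refer the patient for a PCA".

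Protocol article, Percutaneous catheter ablation group: "One hundred patients will be randomized to PCA and treated according to the protocol of the referring center". The rest of that paragraph describes the procedure. For recurrence after blanking, the investigator may choose a "second PCA procedure, surgical ablation, or switch to a rate-control approach", and the last of these is scored as a failed repeated procedure. Antiarrhythmic drugs after ablation are not mentioned.

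Text common to both arms: the Antiarrhythmic therapy section covers only the stop before the procedure. The Methods section refers the inclusion criteria and "the protocols for managing the pharmacologic and anticoagulant therapy" to the 2012 consensus statement and the European guidelines. The abstract likewise bases treatment protocols on the consensus statement and has all patients re-evaluated at three months under the same guidelines.

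Assessment of recurrence: one primary outcome is being free of AF at one year, "as detected by a 12-lead ECG and a 24-hour Holter examination after 3, 6, and 9 months of follow-up"; the other is whether the patient is re-ablated. Neither is defined as on or off antiarrhythmic drug.

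**The concern.** The protocol gives its own reason for the stop: recurrence is to be assessed without drug. That reason applies equally to both arms, but the rule is written in one.

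Both primary outcomes depend on drug status. A drug that suppresses AF raises observed freedom from AF and removes the trigger for a second ablation. The decision to re-ablate is left to the investigator in both arms, no masking is described, and the investigator will know whether the first procedure was surgery or a catheter. The second-procedure contrast is also the one expected to show the difference, because at the end of the interventions "the number of patients in SR should be equivalent in the two groups". If the arms follow different rules on who may stay on drug and how that is scored, part of an observed difference, or of its absence, could come from those rules and not from the first procedure.

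**Working it through.** **1. The arms side by side**

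| Rule after the first procedure | Surgical arm | PCA arm |
|---|---|---|
| Drug during the first 3 months | Permitted | Not stated |
| Drug at month 3 | Must stop | Not stated |
| Recurrence controlled by drug | Continue drug or refer for PCA | Not stated |
| Recurrence, other routes | PCA | Second PCA, surgery or rate control |
| Scoring of rate control | Not stated | Failed repeated procedure |

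The PCA section does repeat other shared rules, such as recording inducibility and allowing cardioversion. The drug stop is not among them.

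**2. What Table 1 assumes**

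The fractions of second procedures equal one minus first-procedure success:
- surgical: 1 − 0.70 = 0.30
- PCA: 1 − 0.35 = 0.65, 1 − 0.45 = 0.55, 1 − 0.50 = 0.50

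So every first-procedure failure is planned as a second procedure. A recurrence kept on drug without ablation breaks that equality, and it is a written option in the surgical arm only.

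The plan's own power reproduces with a two-sided pooled z test at 0.05 (two-sided is an assumption), n = 50 and 100. For 0.30 v 0.65:
- pooled proportion = (50 × 0.30 + 100 × 0.65)/150 = 0.533
- null standard error = √(0.533 × 0.467 × (1/50 + 1/100)) = 0.0864
- alternative standard error = √(0.30 × 0.70/50 + 0.65 × 0.35/100) = 0.0805
- power = Φ((0.35 − 1.96 × 0.0864)/0.0805) = 98.8%, against the stated 99%

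The other two columns give 83.8% and 65.1%, against 84% and 65%. No stated figure is in dispute.

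**3. Direction**

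- A PCA recurrence suppressed by continued drug raises PCA freedom from AF and lowers PCA second procedures. This narrows the difference in second procedures.
- A surgical recurrence kept on therapy lowers surgical second procedures. This widens the difference.
- PCA rate control scored as a failed repeated procedure counts against PCA. No matching rule exists for surgery.

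These effects oppose each other, so no net direction follows.

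**4. Size per patient**

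One patient who recurs and is not re-ablated by month 12 changes the arm's second-procedure fraction by 1/100 = 0.01 (PCA) or 1/50 = 0.02 (surgical). The document gives no number or share of such patients, so no total can be computed.

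**The case against.** The best defence is that one common rule already exists by reference. The abstract and the Methods refer treatment and drug management in the whole trial to a single consensus statement. The PCA section also speaks of the 3-month blanking period without defining it. The rule that recurrences in that period do not count appears only in the surgical section, which suggests that post-ablation rules were written once, in the arm described first. In a condensed article, one unrepeated sentence is weak evidence of a deliberate difference. Treatment under the referring center's protocol may also concern technique alone, since Study limitations says "the choice of the initial technique will be left to the treating cardiologist".

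Much of this stands. A reader might infer that PCA patients will be assessed on drug while surgical patients are off it, and that the bias therefore favours PCA. The document does not support that. Continued drug is not among the PCA routes listed, and the surgical arm is not strictly off drug either. A reader might also work out how far power would fall if a given number of PCA recurrences were held on drug. Any such figure rests on an assumed count and is not evidence of a loss. Nor does the point justify moving the second-procedure decision to month 6, which is a debatable clinical trade-off.

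What the defence does not remove is the explicit difference in the text. The cited source is not at hand, so whether it contains a month-3 stop cannot be checked here. The option to stay on drug and the scoring of rate control are each written for one arm only, and a general reference does not undo that. These are treatment and scoring rules that act at month 3, and an analysis plan could not restore the stop afterwards.

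**Conclusion.** The point holds as an asymmetry in written rules. Followed literally, the protocol allows freedom from AF and second ablation to be judged under different drug rules by arm, and a recurrence managed without re-ablation to be scored differently by arm. It does not show that a difference was intended or that results will be biased by any particular amount. Size and direction are both undetermined.

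The conclusion assumes that investigators follow the article's text and that no common month-3 rule reaches them through the cited consensus statement. If such a rule does, the drug-stop part reduces to a missing sentence, while the unequal drug option and rate-control scoring would still need correcting. The correction is worth making because both primary outcomes are exposed and the change is small.

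**What to change.** 1. State in the PCA section, or once in the shared Antiarrhythmic therapy section, that drugs stop at month 3 in both arms.
2. Allow or disallow continued drug therapy for recurrence equally in both arms.
3. Count a recurrence managed by continued or resumed drug, or by rate control, without re-ablation, as first-procedure failure in both arms.

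The visit schedule and the timing of the second-procedure decision stay as they are.

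**Cost:** a few sentences of protocol wording and no extra visits. Slightly more off-drug recurrences may be detected in the PCA arm than under the present silence. The trial is already recruiting, so the clarification can fully protect only patients who have not yet reached month 3.

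### Recurrence managed without re-ablation follows arm-specific rules: continued drugs in the surgical arm have no stated score, while rate control in the catheter arm counts as a failed repeat

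*Protocol article*

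**What the plan says.** **Surgical arm** (Staged surgical ablation group). Antiarrhythmic drugs may be used for the first 3 months. Then: "At 3 months, they must be stopped to assess recurrences". For a recurrence that drugs control, "it will be left to the preference of the investigator to continue the medical therapy or to refer the patient for a PCA". Nothing says how the patient kept on drugs is scored.

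**Catheter arm** (Percutaneous catheter ablation group). After blanking, the investigator chooses among "a second PCA procedure, surgical ablation, or switch to a rate-control approach. The latter will be counted as a failed repeated procedure". The Methods section says of the control group: "In the case of recurrence of the AF, the second procedure will be either percutaneous or surgical". Continued antiarrhythmic treatment is not among the listed options.

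**Outcome** (Assessment of recurrence). The primary outcomes are freedom from AF at 12 months "and the occurrence of a second ablation procedure". The Statistical analysis section expects rhythm to end up equivalent in the two groups and the second-procedure proportions to differ significantly. It compares patients receiving repeated procedures with a z test and an odds ratio.

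**The concern.** The second-procedure proportion is the primary outcome on which the trial expects to show a difference. A count of ablations performed depends on whether a recurrence occurred and also on what the investigator then chose to do. The article gives that choice different content in each arm. A surgical recurrence can be held on drugs and leave no mark on the count. The only listed way for a catheter recurrence to avoid re-ablation is rate control, which is charged to that arm as a failed repeat. The investigator must know the arm, because the options depend on it. Part of an observed surgical advantage could then come from the management and scoring rules and not from the ablation.

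**Working it through.** **Inputs.** 50 surgical and 100 catheter patients (Abstract). Second-procedure fractions of 0.30 surgical against 0.65, 0.55 or 0.50 catheter (Table 1). First-procedure success of 70% surgical (Statistical analysis). Two-sided 5% level; the article does not state sidedness, so this is assumed.

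**1. The plan's own figures.** With pooled fraction p̄:
- SE0 = √[p̄(1−p̄)(1/100 + 1/50)]
- SE1 = √[pc(1−pc)/100 + ps(1−ps)/50]
- power = Φ[(d − 1.96·SE0)/SE1]

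For 0.65 against 0.30: p̄ = 80/150 = 0.533, SE0 = 0.0864, SE1 = 0.0805, and power = Φ[(0.35 − 0.169)/0.0805] = 98.8%. The other two columns give 83.8% and 65.1%. Table 1 states 99%, 84% and 65%, so its power figures reproduce. The odds ratios come out at 4.33, 2.85 and 2.33 (Table 1: 4.3, 2.9 and 2.33). Table 1 thus treats every first-procedure failure as a second procedure: 1 − 0.70 = 0.30, or 15 of 50.

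**2. Effect of drug management in the surgical arm.** Let k of the 15 surgical failures stay on drugs and go uncounted. The surgical fraction is (15 − k)/50, a fall of 0.02 per patient. First-procedure failure stays at 15/50 in every row. The catheter arm is held at 65, 55 or 50 of 100. The values of k are assumptions that span the possible range.

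| k | Surgical fraction | Differences | Odds ratios |
|---|---|---|---|
| 0 | 0.30 | 0.35, 0.25, 0.20 | 4.33, 2.85, 2.33 |
| 5 | 0.20 | 0.45, 0.35, 0.30 | 7.43, 4.89, 4.00 |
| 10 | 0.10 | 0.55, 0.45, 0.40 | 16.7, 11.0, 9.0 |
| 15 | 0.00 | 0.65, 0.55, 0.50 | not finite |

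For k = 5 in the first column: (65/35)/(10/40) = 1.857/0.25 = 7.43. The z statistics go from 4.05, 2.89 and 2.33 at k = 0 to 5.20, 4.08 and 3.54 at k = 5.

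**3. If catheter patients are also kept on drugs.** Let m of the 65 catheter recurrences stay on drugs uncounted. The difference is (65 − m)/100 − (15 − k)/50 = 0.35 − 0.01m + 0.02k. The gain from k = 5 is cancelled at m = 10, and in general at m = 2k. The direction in step 2 therefore holds when the catheter arm keeps to its listed options.

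**4. Could the rule alone produce a significant result?** Suppose true recurrence r is equal in both arms, every catheter recurrence is scored as a repeat, and a share f of surgical recurrences stays on drugs unscored. The surgical fraction is then r(1 − f). The exact binomial probability that the two-sided pooled z test favors surgery is:

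| f (assumed) | r = 0.65 | r = 0.30 |
|---|---|---|
| 0 | 2.6% | 2.4% |
| 10% | 12.1% | 5.5% |
| 20% | 34.3% | 11.3% |
| 30% | 63.9% | 21.1% |
| 50% | 97.3% | 53.5% |

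**The case against.** The strongest reply is that the two patients are not alike. One still has rhythm control, on drugs. The other has given up sinus rhythm, so calling that a failure is coherent. Also, because drugs are to be stopped at 3 months, first-procedure failure is meant to be seen off drugs, and a recurrence caught on a scheduled ECG or Holter may still count against freedom from AF. This stands, and it narrows the point to the second-procedure outcome. It does not remove it, because that outcome is primary and the article gives a score to only one of the two ways of avoiding re-ablation.

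A reader might infer more than the text supports:
- **That the drug option contradicts the strategy under test.** The Background describes surgery "followed by a second percutaneous procedure in cases of recurrence". But the Methods section defines the surgical strategy with catheter ablation only where needed, and the Abstract attaches the same condition to second procedures generally. Holding a controlled patient on drugs can fit that.
- **That there are two competing outcome definitions.** The Abstract has "the proportions of patients requiring a second procedure", but this is a paraphrase in an abstract. The main-text wording counts procedures performed.
- **That only surgical patients stop drugs at 3 months.** The Methods section draws "The inclusion criteria and the protocols for managing the pharmacologic and anticoagulant therapy" from guidelines for the whole trial, and the Abstract has patients re-evaluated under the same guidelines. The stop plausibly applies to both arms.
- **That catheter patients may not have drugs.** The option is unlisted, not prohibited.

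**Conclusion.** The point holds as an asymmetry in the stated rules. Options after recurrence differ by arm, and only rate control in the catheter arm has an explicit failure score. Under a count of ablations performed, each surgical recurrence kept on drugs moves the surgical fraction down by 0.02 from the planned 0.30 without any gain in rhythm control.

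The actual size is unknown. The article gives no rate of drug use, and the far end of the range would need all 15 surgical recurrences to be drug-controlled. The odds ratios and false-positive probabilities above should not be read as estimates of bias in this trial. They assume k or f, assume no uncounted drug use in the catheter arm, and take rate control there as counted among the repeats. The sample-size arithmetic is not in question. This is a cheap improvement and does not invalidate the design.

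**What to change.** - List the same options after a post-blanking recurrence in both arms: re-ablation, continued antiarrhythmics, or rate control.
- Apply one scoring rule to both arms. Any documented post-blanking recurrence is a failure of the first procedure. Any recurrence managed without re-ablation is scored as the catheter section already scores rate control.
- Report the number of ablations actually performed in each arm alongside, so that the scored outcome is not mistaken for a count of procedures.

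The planned contrast of 0.65 against 0.30 and its power of 98.8% are unchanged, because Table 1 already equates second procedures with first-procedure failures. The change needs protocol wording and slightly more analysis, with no added patients or visits. The price is a somewhat less favorable surgical figure than a bare count of ablations would give.
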